In the study of Mann et al. [43] 96 breast cancer survivors with problematic menopausal HF/NS were randomly assigned to either group CBT or usual care. In this study, women who had received CBT had a significantly reduced HF/NS problem rating as compared to the control group at 9 weeks and at 6 months post-randomization. Our group [44] conducted a 4-group RCT (the EVA trial) to evaluate the efficacy of group CBT, physical exercise (PE), or a combination of CBT and physical exercise in alleviating treatment-induced menopausal symptoms in breast cancer survivors, as compared to a waiting list control group (WLC) (*N* = 422). All intervention groups reported a significant decrease in levels of endocrine symptoms 12 weeks and 6 months after randomization, compared to the usual care waiting list control group. The two groups that included CBT also reported a significant decrease in HF/NS problem rating at 12 weeks and 6 months. However, in the RCT of Duijts and colleagues, noteworthy problems were observed in compliance with the group CBT. More than 50% of women attended less than 4 of the 6 CBT sessions. Many women reported scheduling conflicts related to work and child care as the reason for their under-compliance. Per-protocol analysis suggested that, if compliance rates could be increased, the intervention would be even more effective. Many women indicated an interest and willingness to undergo a CBT program administered via the Internet. This was viewed as a more flexible alternative to face-to-face group CBT, and thus is hypothesized to result in increased compliance and increased efficacy of the treatment. Further, two-thirds of breast cancer patients believe that Internet-based therapy is equally or more likely to result in improved physical and mental health, as compared to face-to-face therapy [50].

A cost-effectiveness analysis (CEA) of the EVA-trial data showed that CBT was likely to be the most cost-effective intervention, with incremental cost-utility ratios of €22,502/quality adjusted life year (QALY) for CBT versus WLC and €28,078/QALY for PE versus WLC [51]. Providing CBT via an Internet-based platform, either in a guided or self-managed format may further increase the cost-effectiveness of this intervention.

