	▪ In-session assignment: identification of stressful events, usual reaction to stress and goal setting to reduce stress
	▪ Homework: as before + implementation of stress goal
Module 4 Improving sleep	▪ Psycho-education about sleep, sleeping problems and how to improve quality of sleep, cognitive and behavioral reactions to sleep problems/night sweats.
	▪ In-session assignment: sleep hygiene questionnaire, goal setting to improve sleep.
	▪ Homework: as before + implementation of sleeping goals
Module 5 My body and sexuality	▪ Psycho-education about sexual problems and weight issues, cognitive and behavioral precipitants and consequences of sexual problems and weight issues.
	▪ In-session assignment: goal setting for sexual problems (if present) and weight issues (if present)
	▪ Homework: as before + implementation of goals
Module 6 Keep progressing	▪ Psycho-education about the (benefits of) using an action plan.
	▪ In-session assignment: identification of helpful cognitive and/or behavioral strategies as discussed/learned throughout each module, goal setting for maintenance plan; identification of possible barriers and how to overcome them.
	▪ Homework: as before + implementation of maintenance plan

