#### Waiting list control group

Participants in the waiting list control group are offered the opportunity to follow the CBT program after completion of the 6-month follow up questionnaire. There are no other behavioral interventions for menopausal symptoms available through the participating hospitals, but women in all groups are asked at the follow-up assessments if they engaged in any other means to reduce their menopausal symptoms.

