#### Outcome measures

A detailed description of the outcome measures is provided in Table 2. Briefly, the primary outcome measures include standardized self-report questionnaires assessing hot flushes and night sweats problem rating using the Hot Flush Problem Rating Scale (HFRS) [69], and overall levels of menopausal symptoms using the Functional Assessment of Cancer Therapy –Endocrine symptom scale (FACT-ES) [72]. Secondary outcome measures include standardized self-report questionnaires assessing sexual functioning (SAQ) [73], sleep quality (GSQS) [74]; hot flush frequency (HFRS) [69], psychological distress (HADS) [75, 76] and health-related quality of life (SF-36 Health Survey) [77, 78].

**Table 2 Tab2:** Study outcome measures and corresponding questionnaires

Variable	Questionnaire	Details
Primary outcomes		
Hot flush/Night sweats problem rating	HFRS	▪ 3 items (subscale), 10 point scale
		▪ Score range: 0–10 (mean scores are used); higher scores indicate higher problem rating
		▪ Time frame: 1 week
		▪ Test-retest reliability 0.80
Overall level of menopausal symptoms	FACT-ES	▪ 18 items, 4 point Likert scale
		▪ Score range: 0–72; higher scores indicate fewer menopausal symptoms
		▪ Time frame: 1 week
		▪ Cronbach’s alpha: >0.80
Secondary outcomes		
Sexual functioning	SAQ	▪ 10 items, 4 point Likert scale
		▪ Subscales: pleasure; discomfort; habit
		▪ Score range: pleasure 0–18 higher scores indicate higher levels of pleasure; discomfort 0–6 lower scores indicates lower levels of discomfort; habit 0–3; single item (0 ‘less sexual activity than usual’ to 3 ‘much more sexual activity than usual’
		▪ Time frame: past month
		▪ Test-retest kappa: 0.50–0.76
Sleep quality	GSQS	▪ 14 items, dichotomous (yes/no) scale
		▪ Score range: 0–14; higher scores indicate more sleep problems
		▪ Time frame: past month
Hot flush frequency	HFRS	▪ 2 items (subscale); open-ended frequency scale
		▪ Score range: reported average of HF/NS per week
		▪ Time frame: past week
		▪ Test-retest reliability 0.80
Psychological distress	HADS	▪ 14 items, 4-point Likert scale
		▪ Subscales: depression (HADS-D); anxiety (HADS-A)
		▪ Score range: total score 0–42; subscale scores 0–21 higher score indicates more psychological distress
		▪ Time frame: past week
		▪ Cronbach’s alpha: HADS-D 0.67–0.90; HADS-A 0.68–0.93
Health-related quality of life	SF-36	▪ 36 items, dichotomous and 3- to 6-point Likert scales

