#### Compliance with the intervention

Women are asked to indicate the number of CBT program modules they completed, the frequency with which they did the homework assignments and the total amount of time (in weeks) that they used the program. We are also able to monitor the actual use (frequency and duration) of the online CBT program through log data. We consider completion of the first three modules evidence of an acceptable level of program compliance because these are the modules that specifically focus on the primary outcomes.

Women who do not complete the intervention are asked to indicate their reason(s) for discontinuation (e.g., lack of motivation, illness, program burden). We assess general self-efficacy, social support and intention to complete the program as potential predictors of compliance. General self-efficacy is measured with the General Self-Efficacy scale from [82]. It includes 10 items (4 point Likert scale). Social support is assessed by the emotional/informational support subscale (8 items Cronbach’s alpha 0.96) of the Medical Outcome Study- Social Support Scale ((MOS-SS [83]). Behavioral intention is assessed by three items (5 point Likert scale) derived from the Theory of Planned Behavior [84].

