### Statistical analysis

All data will be anonymized prior to final data analysis. The data set will not contain any personal identifiers. Only study staff will have access to these data.

Analyses will first be performed to evaluate the comparability of the intervention groups (guided versus self-management) and control group at baseline in terms of sociodemographic and clinical characteristics. ANOVA tests or appropriate non-parametric statistics will be used, depending on the level of measurement. If, despite the stratified randomization procedures, the groups are found not to be comparable on one more background variables, those variables will be employed routinely as covariates in subsequent analyses. Questionnaire scores will be calculated according to published scoring algorithms. We will compare both intervention groups with the control group over time using multilevel procedures with repeated measures, using a restricted maximum likelihood (REML) solution to model specific contrasts between groups and follow-up assessment [89]. Within each multilevel model the control group will be the reference category. For the analysis of the secondary outcome measures, appropriate statistical adjustments will be made for multiple testing. Differences in mean change scores over time between the intervention groups and the control group will be accompanied by effect sizes (ES). These effect sizes will be calculated using standard statistical procedures. Effect sizes of approximately 0.5 are considered clinically significant [90]. All analyses will be conducted on an intention to treat (ITT) basis. In addition, per-protocol (PP) analyses will be performed (as a secondary analysis) on patients who met criteria for minimal compliance with the intervention(s). Supplementary analyses will be carried out in which data relating to compliance with the program elements will be taken into account. Specifically, we will determine whether the level of compliance is associated significantly with the change over time in the primary and secondary outcomes. We will also investigate whether program effectiveness varies significantly as a function of changes in hot flush beliefs and behaviors.

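### The secondary per-protocol analysis selects women on module completion that only the CBT arms can show, so its contrast with control is not randomised and can be biased

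*Protocol article*

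**What the plan says.** Under Statistical analysis the protocol article makes intention to treat the basis: "All analyses will be conducted on an intention to treat (ITT) basis". It then adds that "per-protocol (PP) analyses will be performed (as a secondary analysis) on patients who met criteria for minimal compliance with the intervention(s". Supplementary analyses will test whether level of compliance is associated with change in the primary and secondary outcomes. The Current study section describes compliance as a moderator to be explored.

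The criterion is under Compliance with the intervention: "We consider completion of the first three modules evidence of an acceptable level of program compliance". The reason given is that "these are the modules that specifically focus on the primary outcomes". Table 1, however, lists under module 4 "cognitive and behavioral reactions to sleep problems/night sweats", and night sweats are part of the first primary outcome, the problem rating for hot flushes and night sweats.

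On the control arm the article says: "Participants in the waiting list control group are offered the opportunity to follow the CBT program after completion of the 6-month follow up questionnaire". It does not say how controls enter the per-protocol set.

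**The concern.** Completing three modules happens after randomisation and can be observed only in the two CBT arms. Women who complete may differ in prognosis from those who do not. The article itself measures self-efficacy, social support and intention as possible predictors of compliance, and names lack of motivation, illness and program burden as reasons for stopping. No matching subset of controls can be picked out, so a difference in prognosis enters the contrast directly.

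The two supplementary analyses share the problem. Within a CBT arm, an association between modules completed and improvement mixes the effect of the program with the kind of woman who completes it. As a moderator, compliance is not defined in controls, so an ordinary arm-by-compliance interaction cannot be formed.

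What is at stake is interpretation. The Background reads the earlier group trial's per-protocol result as a sign that better compliance would raise efficacy, and that reasoning motivates the Internet format. The same inference is likely to be drawn from this trial, even if completers simply had the better outlook.

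**Working it through.** **The plan's own figure.** The Power calculation section gives 66 per group, 0.5 SD, two-sided 0.05 and 80% power. A noncentral t calculation gives 81%, and 198 / 0.8 = 247.5, rounded up to 248. Both reproduce, and the per-protocol question does not affect them.

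**Inputs.** From the article: 66 analysed per arm, a 0.5 SD effect, no control access before the 6-month questionnaire. Assumed, because the article gives neither: c (proportion compliant in a CBT arm) and δ (extra improvement, in SD, that compliers would have had without the program). Also assumed: all controls stay in the per-protocol set.

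**Bias.** Let τ be the true effect in compliers and m the mean untreated improvement of non-compliers.

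- Treated compliers: m + δ + τ
- All controls, a mixture of would-be compliers and non-compliers: m + cδ
- Per-protocol difference: τ + (1 − c)δ

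| c | δ = −0.2 | δ = 0 | δ = 0.2 | δ = 0.3 | δ = 0.5 |
|---|---|---|---|---|---|
| 0.5 | −0.10 | 0 | 0.10 | 0.15 | 0.25 |
| 0.7 | −0.06 | 0 | 0.06 | 0.09 | 0.15 |

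With τ = 0.50, the positive δ values give per-protocol estimates of 0.60 to 0.75 at c = 0.5 and 0.56 to 0.65 at c = 0.7.

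**Second model.** Let compliance propensity correlate ρ with untreated improvement, so that the shift is ρ × φ(z) / c, with φ the normal density at the cut-off z. With no true effect and ρ of 0.1 to 0.3:

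- c = 0.5: 0.08 to 0.24 SD, two-sided rejection 7% to 20%
- c = 0.7: 0.05 to 0.15 SD, 6% to 12%
- c = 0.9: 0.02 to 0.06 SD, 5% to 6%

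At ρ = 0 the shift is zero. At ρ = −0.2 and c = 0.5 it is −0.16 SD.

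**Effect of the cut-off.** At fixed positive δ, (1 − c)δ falls as c rises. A lower module threshold cannot reduce c, so by this formula it does not enlarge the bias.

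**CACE.** Non-compliance is one-sided. If women below the threshold gain nothing, the intention-to-treat difference is cτ, and dividing by c returns τ whatever δ is. Approximate standard errors, treating c as known:

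- c = 0.5: per-protocol √(1/33 + 1/66) = 0.21; CACE √(2/66) / 0.5 = 0.35; ratio about 1.6
- c = 0.7: per-protocol √(1/46.2 + 1/66) = 0.19; CACE √(2/66) / 0.7 = 0.25; ratio about 1.3

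In simulation, where c also varies, the ratios were about 1.7 and 1.3, and the mean CACE stayed at about 0.49 to 0.50.

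**Where CACE fails.** If women below the threshold gain p, the estimate is [cτ + (1 − c)p] / c. With τ = 0.5 and an assumed p of 0.25:

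- c = 0.5: (0.25 + 0.125) / 0.5 = 0.75
- c = 0.7: (0.35 + 0.075) / 0.7 = 0.61

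So a CACE at a partial-completion threshold can be as far off as the per-protocol estimate it replaces. Defining exposure as any program use largely removes this, because few of the women counted as unexposed can then have benefited.

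**The case against.** The strongest reply is that the article already limits these analyses. Intention to treat is the stated basis, women who stop the program but complete follow-up stay in the analysis, the per-protocol analysis is labelled secondary, and the compliance work is labelled supplementary or exploratory. No primary claim or sample size rests on them. That stands, and it limits the severity. It does not settle how the per-protocol figure will be read, given the Background's use of the earlier one.

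A second reply is that neither c nor δ is in the article, and that handling of controls is commonly left to the analysis plan. Both are fair. The sizes above are conditional, and the missing rule for controls is not itself a fault. What remains is that the stated selection criterion cannot apply to controls under any rule.

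A third reply is that CACE brings its own assumption. This also stands, and it is why the 3-module threshold should not be the main exposure.

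A reader might go further and infer that the 3-module cut-off contradicts a benchmark of four sessions from the earlier trial. The Background says only that "More than 50% of women attended less than 4 of the 6 CBT sessions". That is an attendance figure for face-to-face groups, not a compliance criterion. A reader might also infer that the low cut-off causes the overstatement; the formula points the other way. Nor does Table 1 overturn the stated reason for three modules. Module 2 is on hot flushes, modules 1 and 3 contribute the symptom diary, relaxation and the link between stress and flushes, and a specific focus there does not exclude later modules. The night-sweats content of module 4 makes the reason loosely worded, no more.

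**Conclusion.** The point holds for the per-protocol contrast and the compliance associations: they are not protected by randomisation, and the article specifies nothing that would restore comparability. If compliers would have improved more anyway, the per-protocol analysis overstates the effect by (1 − c)δ. For the assumed values this is 0.06 to 0.25 SD, or 12% to 50% of the 0.5 SD design effect (0.06/0.5 and 0.25/0.5). That it must overstate is not supported: the bias vanishes at δ = 0 and reverses for negative δ, and the article gives no basis for fixing δ. The sizes also assume that all controls are kept. The intention-to-treat analysis and the sample size are unaffected.

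**What to change.** - Estimate the effect under use by a CACE for each CBT arm versus control, with randomised arm as instrument and log-recorded use as exposure. Take any program use, or number of modules completed, as the main exposure, and keep the stated 3-module cut-off as a sensitivity analysis. The number-of-modules version gives an effect per module, which needs a linear dose response to be read across the whole program.
- If the per-protocol analysis is retained, keep all controls in it. Report it and the within-arm compliance associations as non-randomised, and not as evidence that better compliance raises efficacy.
- Reconcile the reason given for three modules with Table 1, where module 4 also covers night sweats.

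The cost is a few sentences and one extra model; the log data are already collected. The CACE interval is wider: at the c values used here, its standard error is about 1.3 to 1.7 times that of the per-protocol estimate. It also relies on allocation having no effect except through the chosen exposure. In the guided arm the telephone interview before the program strains this slightly, so the plan should say whether the interview counts as use.

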### Current study

This randomized, controlled, multicenter trial, “EVA-Online”, is designed to evaluate the efficacy and cost-effectiveness of two Internet-based CBT programs, one guided and the other self-managed, to reduce or ameliorate treatment-induced menopausal symptoms in women who have had breast cancer. We hypothesize that women in both Internet-based CBT groups will report a significantly greater reduction in overall levels of menopausal symptoms and/or HF/NS problem rating than women in the control group. Secondarily, we hypothesize that women in both Internet-based CBT groups will report significantly greater improvement in sexual functioning, sleep quality, hot flush frequency, psychological distress and HRQOL than women in the control group. We will also evaluate the relative efficacy of self-managed versus guided Internet-based CBT, but this will be done in a more descriptive manner, given that the trial is not powered to test these differences formally. We are also investigating, in a more exploratory manner, the extent to which program compliance serves as a moderator, and hot flush beliefs and behavior as mediators of the treatment effects on the primary outcomes of interest [68]. Finally, we hypothesize that both internet-based CBT groups have a higher probability of being cost-effective compared to the control group. If demonstrated to be efficacious and cost-effective, the availability of such structured supportive intervention programs will be a welcome addition to standard medical treatment offered to cancer survivors with treatment-induced menopause.

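### Observed programme compliance cannot be a moderator of the CBT-versus-control effect, because it arises after randomisation and has no value in the waiting-list arm; the planned significance test answers a different, confoundable question

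*Protocol article*

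**What the plan says.** All references are to the Protocol article.

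- **Current study** sets the aim. It is introduced with "We are also investigating, in a more exploratory manner", and the object is "the extent to which program compliance serves as a moderator, and hot flush beliefs and behavior as mediators of the treatment effects". The effects meant are those on the two primary outcomes.
- **Compliance with the intervention** defines the variable: "Women are asked to indicate the number of CBT program modules they completed, the frequency with which they did the homework assignments", together with weeks of use and log data from the online programme. The same section adds: "We assess general self-efficacy, social support and intention to complete the program as potential predictors of compliance". It does not say when those three scales are administered or in which arms.
- **Waiting list control group** says that controls are "offered the opportunity to follow the CBT program after completion of the 6-month follow up questionnaire".
- **Statistical analysis** gives the method. It begins "Supplementary analyses will be carried out in which data relating to compliance with the program elements will be taken into account" and then specifies that "we will determine whether the level of compliance is associated significantly with the change over time in the primary and secondary outcomes". It names no interaction with arm and no adjustment for determinants of compliance.

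**The concern.** A moderator of the CBT-versus-control effect is a characteristic across whose levels the difference between arms can be compared. It therefore has to be defined in both arms, and ordinarily before treatment starts. Observed compliance fails on both counts: it comes into being only after allocation, and only where there is a programme to comply with. The aim in Current study and the test in Statistical analysis therefore concern different quantities.

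The test that can be run compares women who used the programme more with women in the CBT arms who used it less. Nobody was randomised to a level of use. The plan itself expects use to depend on self-efficacy, support and intention, and lists low motivation and illness among possible reasons for stopping. Any of these could also bear on symptom change.

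What is at stake is a central part of the rationale. Background argues that Internet delivery should raise compliance and, through it, efficacy, and cites a per-protocol result from the earlier group-CBT trial as suggesting that better compliance would mean a larger effect. A significant association labelled as moderation could be cited as confirming that argument, although the analysis cannot separate it from differences between the women who persist and those who do not.

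**Working it through.** **1. The plan's own figures.** Power calculation states 66 women per group followed, 0.5 SD, two-sided 0.05 and 80% power. Recomputation gives 82% by the normal approximation and 81% by the noncentral t with 130 degrees of freedom. Recruitment: 198 / (1 − 0.20) = 247.5, rounded up to 248, as stated. These figures are sound. The number used below is 2 × 66 = 132 CBT women followed.

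**2. Can the moderation term be estimated?** Write A for arm (0 control, 1 CBT) and C for compliance. Moderation is the coefficient of A × C in

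change = b0 + b1·A + b2·C + b3·A·C + error.

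- *Controls coded C = 0.* For controls, C = 0 and A·C = 0. For CBT women, A·C = C. The columns C and A·C are identical in every row, so the four-column design matrix has rank 3. Only b2 + b3 can be estimated, and it is the slope of change on compliance among CBT women.
- *Controls coded missing.* They drop out, and no control contrast remains.

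Either way, the data yield a slope within the CBT arms and no estimate of b3. More model detail would not alter this for observed compliance.

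**3. How often would a non-causal association be called significant?** The documents give no correlation between compliance and change, so r is an assumption, shown over a range. By Fisher's z with n = 132, the noncentrality is atanh(r) × √(132 − 3) = atanh(r) × 11.36, and the rejection probability is approximately Φ(noncentrality − 1.96).

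| Assumed r | atanh(r) | Noncentrality | P(significant) |
|---|---|---|---|
| 0.1 | 0.100 | 1.14 | 0.21 |
| 0.2 | 0.203 | 2.30 | 0.63 |
| 0.3 | 0.310 | 3.52 | 0.94 |

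**4. Could such correlations arise with no dose effect and no moderation?** This was checked by simulation: 4,000 trials per setting, 66 controls and 132 CBT women, and the same 0.5 SD benefit for every CBT woman whatever her use. One unmeasured prognostic factor is correlated 0.5 with latent compliance (assumed), which is then scored as 0 to 6 modules.

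| Assumed correlation of factor with change | Mean r, compliance with change | P(significant) |
|---|---|---|
| 0 | 0.00 | 5% |
| 0.2 | 0.10 | 21% |
| 0.3 | 0.14 | 38% |
| 0.4 | 0.19 | 61% |
| 0.5 | 0.24 | 80% |

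With no shared factor the test keeps its nominal 5%. With one, it rejects more often although extra modules do nothing. The strongest setting reaches a mean r of 0.24, so the r = 0.3 row in step 3 lies beyond anything produced here.

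**The case against.** The strongest reply is that the operative sentence claims little. Statistical analysis speaks of an association and says nothing of moderation, dose-response or cause. The word moderator is attached to compliance in an aim marked as exploratory, and the analysis is called supplementary. The article also condenses a fuller protocol, and covariates for a supplementary model are commonly left to that document or to the SAP. All of this stands, and it limits the priority of the point. It does not remove it: the mismatch between the stated aim and the stated test is in the article, and step 2 shows that further detail cannot make observed compliance an identified moderator.

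Three stronger readings are tempting and should not be drawn.

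- *That the trial will report a confounded dose-response.* Nothing commits the authors to a causal reading, and the size of any confounding is unknown.
- *That 63% and 94% are false-positive rates of the stated test.* They are the power of a correlation test at an assumed r. If the question is only whether an association exists, rejecting is correct. The figures mislead only if the result is read as an effect of compliance.
- *That women who see no benefit stop.* The documents do not say so. The example reasons for stopping are lack of motivation, illness and programme burden, and the earlier trial's under-compliance is attributed to scheduling conflicts. In the guided arm the next module opens after feedback has been received and read, so access there depends on feedback, not on symptom response.

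**Conclusion.** The point holds as a mismatch of modest weight between an exploratory aim and its analysis. That observed compliance cannot be identified as a moderator of the CBT-versus-control effect follows from the article's own definitions and needs no numerical assumption. That the within-CBT association is open to confounding follows because compliance is not randomised and its expected determinants may also affect outcome. How large the confounding is cannot be known from the documents; the 21% / 63% / 94% illustration rests entirely on the assumed correlations and on 132 women followed. The primary intention-to-treat comparison, the sample size and the main conclusions are not touched. The correction is worth making because it costs almost nothing and removes an inference that would otherwise lend support to the trial's compliance rationale.

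**What to change.** 1. In **Current study**, stop describing observed compliance as a moderator. State the aim as describing how programme use relates to change among women allocated to CBT.
2. In **Statistical analysis**, replace the significance test with a descriptive report of the compliance-change association within the CBT arms. Present it separately for the guided and self-management arms, since modules are released differently in each, and adjust for the measured predictors of compliance. Give an estimate with its confidence interval, make no claim of significance, and state that the association is not causal.

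This needs wording changes only and no new data. Estimates by arm will be imprecise: with 66 women the 95% interval is about ±1.96 / √63 = ±0.25 on Fisher's z scale, before adjustment.

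3. *Optional and conditional.* If the self-efficacy, social support and intention scales were collected at baseline in all three arms, a score predicting compliance could be fitted in the CBT arms, computed for every woman, and its interaction with arm explored. The article does not state this, and its list of baseline sociodemographic and clinical items does not include these scales, so it must be confirmed first. The report should say that precision will be low, that the uncertainty of the first-stage model has to be carried through, and that the analysis concerns modification by baseline propensity to comply, not by compliance received. The cost is one extra model.

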### Moderating and process measures

#### Hot flush beliefs and behaviors

Beliefs about hot flushes and night sweats are considered moderators of the effect of the CBT program [79]. These are assessed with the Behavior Short Form HFNS Beliefs and Behavior Scale, a 16 item scale that includes items from the Hot Flush Beliefs Scale [80] and the Hot Flush Behavior Scale [81], ([name], personal communication).

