### Power calculation

The HFRS problem rating scale and the FACT-ES scale score, assessing endocrine symptoms, are the primary outcomes on which sample size calculations are based. With a total sample of 198 women (66 per group), and under the assumption of no interaction, the study will have 80% power to detect a 0.5 standard deviation difference (Cohen’s effect size) with a p value of 0.05 (two sided test) [88]. We anticipate that this effect size will be sufficient to demonstrate the efficacy of the interventions, as the CBT group intervention in the EVA-study yielded effect sizes for the primary outcomes of approximately 0.5 [44]. We will recruit 248 women into the study, to allow for an attrition rate of approximately 20% (i.e. women who discontinue participation in the study entirely, including failure to complete follow up questionnaires). Women who discontinue participation in one of the intervention groups but complete the follow up assessments will be included in the analysis.

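### Hot flush beliefs are called mediators in one section and moderators in another, and the one stated analysis (effect against post-randomisation change) cannot support a conclusion on mechanism

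*Protocol article*

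**What the plan says.** Three sections of the protocol article bear on this.

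- **Current study** words one of its exploratory aims as follows: "program compliance serves as a moderator, and hot flush beliefs and behavior as mediators of the treatment effects". The outcomes concerned are the primary ones. The two roles are kept apart here: compliance has one, beliefs and behaviour the other.
- **Hot flush beliefs and behaviors**, under the parent heading "Moderating and process measures", states: "Beliefs about hot flushes and night sweats are considered moderators of the effect of the CBT program".
- **Statistical analysis** gives one supplementary analysis for these variables: to investigate "whether program effectiveness varies significantly as a function of changes in hot flush beliefs and behaviors".

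The article describes no path from arm to beliefs, no path from beliefs to outcome given arm, no indirect effect and no interaction with baseline beliefs. The aim is introduced as exploratory: "We are also investigating, in a more exploratory manner".

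**The concern.** A moderator is a characteristic fixed before randomisation, and it is tested as baseline value by arm. A mediator is something the treatment changes and through which it then acts, and it is tested by an indirect effect. The article assigns beliefs to both roles, so an analyst working from it cannot tell which question is meant.

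The stated analysis does not settle the matter. That effectiveness varies as a function of something is moderation language, but the something is a post-randomisation change that CBT is designed to bring about. Taken one way, the test can report no role for beliefs when they carry the whole effect. Taken another way, it can present a non-causal association as a mechanism. The process conclusion is at stake; the efficacy conclusion is not.

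**Working it through.** **1. The plan's own figures.** The Power calculation section states that "the study will have 80% power to detect a 0.5 standard deviation difference" with 66 per group at two-sided 0.05. With equal arms, power = Φ(0.5 × √(66/2) − 1.96) = Φ(2.872 − 1.960) = Φ(0.912) = 0.82. Recruitment is 198/0.80 = 247.5, so 248. Both reproduce and neither is disputed. The article gives no figure for mediation or moderation.

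**2. The literal reading, by algebra.** Let T be arm, M the change in beliefs and Y the outcome, with M = aT + e and Y = c′T + bM + e. At any given change m, the difference in Y between arms is c′, whatever m is. The arm-by-change interaction is therefore exactly zero. Under full mediation (c′ = 0) the effect at fixed change is also zero, although the total effect is a × b.

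**3. The literal reading, by simulation.** One CBT arm against control, 66 per arm, 5,000 runs, two-sided 0.05, c′ = 0, residual variance of Y set to 1 − b² so that its within-arm SD is 1. The path sizes are assumed; each pair gives a × b = 0.5 SD, the effect the trial is powered for.

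| a | b | Total effect found | Paths a and b both significant | Arm-by-change interaction significant |
|---|---|---|---|---|
| 1.0 | 0.5 | 82.1% | 100.0% | 5.3% |
| 0.8 | 0.625 | 81.4% | 99.5% | 4.9% |
| 0.7 | 0.714 | 80.8% | 97.5% | 5.5% |
| 0.625 | 0.8 | 81.1% | 94.5% | 4.8% |

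The interaction rejects at its false-positive rate throughout. With partial mediation (a = 0.6, b = 0.5, c′ = 0.1) the pattern is the same: 4.5% to 5.5% for the interaction, 92% to 93% for the joint test.

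**4. What the interaction does detect.** Suppose CBT does not move beliefs (a = 0, so no mediation) but the slope of outcome on change differs by arm (b = 0.3, c′ = 0.5, interaction 0.5). The interaction is then significant in 83% of runs and the joint test in 5%. It answers a different question.

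**5. The looser reading.** Take the sentence as an association between change in beliefs and outcome within a CBT arm. Under full mediation it is positive in 99% to 100% of runs. With a = 0 and b = 0.5, so that CBT does not change beliefs and no mediation exists, it is still positive in 97% to 99%, depending on the residual variance assumed. It does not separate the two cases.

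**6. A check on the remedy.** It is natural to regress the T2 outcome on T1 beliefs and adjust for the T1 outcome to secure time order. But the program runs 6 weeks and T1 is at 10 weeks, so much of the effect may already be in the T1 outcome. Take a fully mediated effect with beliefs shifted by 0.6, slope 0.5, and T2 outcome = 0.8 × T1 outcome + noise. The indirect effect on T2 is 0.6 × 0.5 × 0.8 = 0.24, yet given the T1 outcome the path from T1 beliefs to T2 is zero. Detection was 5.3% with the adjustment and 96% without. Across the assumed scenarios that were run, it was 5% to 39% with and 88% to 96% without.

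**The case against.** The strongest reply is that Statistical analysis gives one condensed sentence with no model, interaction term or time point. It follows a compliance analysis described only as an association, and it may be loose wording for the mediation aim in Current study. A journal article may leave the mediation model to the full protocol or analysis plan. This stands in part: the missing indirect-effect model is not a fault in itself, and the article does not commit to an interaction test. What remains is that the current text contradicts itself on the role of beliefs, and that neither natural reading of the stated analysis identifies mediation. A fuller analysis plan would still have to choose between conflicting sections.

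It can also be said that simulating data without an interaction and then finding none is circular. The simulation only illustrates the algebra in step 2, and the point is that full linear mediation implies no interaction. If the belief-outcome slope differed by arm, the interaction could be significant.

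The moderator sentence names only beliefs, and its parent heading also covers process measures. That narrows the conflict to beliefs but does not remove it, since Current study includes beliefs among the mediators.

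A reader might infer that the trial cannot answer its process question at all, or that its efficacy results are in doubt. The documents support neither. The scale is collected, a mediation model can still be specified, the aim is exploratory, and no efficacy test or sample size depends on it.

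**Conclusion.** The concern holds in a limited form. The roles given to hot flush beliefs contradict each other, and the stated process analysis cannot support a conclusion on mechanism. Under the literal reading it rejects at about 5% even when beliefs carry the whole effect; this rests on a linear slope equal in both arms and on assumed path sizes. Under the within-arm reading it is positive in 97% to 99% of trials where CBT leaves beliefs unchanged. The flat statement that the plan would miss full mediation goes too far, because the wording does not fix an interaction model. The 94% to 100% for the joint test comes from a model with a single post-randomisation time point and no baseline covariates; it is a contrast, not a power figure for the analysis proposed below. Severity is low to moderate: worth correcting before analysis, with no bearing on the primary or secondary efficacy tests.

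**What to change.** - Make Current study, Hot flush beliefs and behaviors, and Statistical analysis agree by calling beliefs and behaviour mediators throughout.
- Replace the sentence in Statistical analysis with an indirect-effect analysis: arm to T1 beliefs/behaviour, and T1 beliefs/behaviour to outcome given arm, both adjusted for T0 mediator and T0 outcome, with a bootstrap confidence interval for the indirect effect.
- Do not adjust for the T1 outcome in the main mediation model. Use that adjustment only as a sensitivity analysis for time order.
- If moderation is also of interest, test T0 beliefs by arm as a separate analysis.
- State that the mediation estimate assumes no unmeasured confounding between mediator and outcome. Randomisation does not protect that path.

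The cost is wording and one exploratory model. No new data are needed if the beliefs and behaviour scale is collected at T0 and T1. This is an assumption: the article gives no separate schedule for the scale, although an analysis of changes implies at least two measurements.
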